#### Maternal-child sensitivity (MORS-SF)

In the absence of a minimum clinically important difference for the MORS-SF, we based our sample size calculations on 0.5 of a standard deviation in the MORS-SF [16]. A recent study of a trial delivered in Better Start Bradford indicates that the standard deviation in the MORS-SF is 4.7 [9]. We will have 80% power to detect 0.5 of this difference in the MORS-SF (± 2.35, *d* = 0.50) with 130 participants total (65:65), or if we obtain a larger control group through the BiBBS additional sweep (e.g. 140 total (56:84), 150 total (50:100), 180 total (45:135)). Historical data from Baby Steps in Bradford indicate that there is approximately a 40% attrition rate between enrolling and completing the project. To detect a difference in the MORS-SF, Baby Steps should therefore aim to enrol at least 72 participants to achieve the minimum sample size of 45 participants in the intervention group at the end of the study.

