**Methods:**

The study is a quasi-experimental evaluation in a single centre. All participants are drawn from Born in Bradford’s Better Start (BiBBS) interventional family cohort study. Intervention participants will be matched to a demographically comparable control group using propensity score matching. The required minimum sample is *n* = 130 (ratio 1:1) to detect a medium effect (± 2.35, *d* = .50) on the primary outcome—maternal-child sensitivity, using the Mothers Object Relations Scale Short Form (MORS-SF). Secondary outcomes include the Patient Health Questionnaire (PHQ-8), Generalised Anxiety Disorder assessment 7 (GAD-7), identification of poor perinatal mental health through routine data, and birth outcomes (delivery method, gestation period, low birth weight). Service delivery costs and health resource use will be gathered from routine data.

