### Sample size calculations

Sample size calculations for our primary and secondary outcomes were produced using Stata-17’s *power* command for the effectiveness outcomes. Sample size calculations were based on two sample means t-test with a two-tailed alpha of 5%.

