#### Maternal mental health (GAD-7 and PHQ-8)

Recent studies have estimated the minimum clinically important difference in the PHQ-9 to be 2 points [5, 32]. The sample size calculations show that we will have 80% power to detect this difference in the PHQ-8 and GAD-7 (± 2, *d* = 0.42) with 190 participants total (95:95), or if we obtain a larger control group through the BiBBS cohort (e.g. 200 total (80:120), 210 total (70:140), 250 total (62:187)). With the 40% attrition rate, Baby Steps should aim to enrol at least 99 participants to achieve the minimum sample size of 62 participants at the end of the study. We have therefore recommended to Baby Steps that they aim to recruit 99 intervention participants overall, as after accounting for attrition, this study should have statistical power to detect a minimum clinically important difference in all measures (MORS-SF, PHQ-9, GAD-7).

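### At the protocol's own 40% attrition, enrolling 72 and 99 leaves about 43 and 59 intervention women, not the stated 45 and 62; the effect on power is small

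*Protocol article*

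**What the plan says.** All places are in the protocol article.

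- **Sample size calculations.** The basis is given as follows: "Sample size calculations were based on two sample means t-test with a two-tailed alpha of 5" percent.
- **Maternal-child sensitivity (MORS-SF).** For want of a minimum clinically important difference, "we based our sample size calculations on 0.5 of a standard deviation in the MORS-SF", and a recent local trial "indicates that the standard deviation in the MORS-SF is 4.7". Four splits are listed for 80% power: 65:65, 56:84, 50:100 and "180 total (45:135"). Attrition from enrolling to completing is put at approximately 40%, from historical data. The conclusion is that "Baby Steps should therefore aim to enrol at least 72 participants to achieve the minimum sample size of 45 participants" in the intervention group.
- **Maternal mental health (GAD-7 and PHQ-8).** For a 2-point difference (d = 0.42) the splits are 95:95, 80:120, 70:140 and 62:187. Applying the 40% rate, "Baby Steps should aim to enrol at least 99 participants to achieve the minimum sample size of 62 participants". The service has been advised to recruit 99. The closing sentence says that, after attrition, this should give power for a minimum clinically important difference on all three measures, the MORS-SF among them.
- **Abstract, Methods.** The required minimum sample is "130 (ratio 1:1) to detect a medium effect" on the MORS-SF.
- **Linear regression analyses.** The intention-to-treat analysis takes all mothers enrolled after the initial home visit. The per-protocol analysis takes only completers.

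**The concern.** If a fraction d of enrolled women is lost, the number left is enrolled × (1 − d), so the enrolment needed is n / (1 − d). Neither 72 nor 99 satisfies this at d = 0.40. These are finished figures, not details left for an analysis plan: 99 has already been given to the service as its target, and the claim of adequate power on every measure rests on it.

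Two features make the figures easy to misread. First, 45 and 62 are each called the minimum sample size, but each is the intervention arm of the most control-heavy split listed, at about three controls per intervention woman. The enrolment sentences do not repeat that condition. Second, the 40% is loss from the programme, not from outcome measurement, and the text does not say which analysis the inflated target is meant to protect.

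**Working it through.** **Inputs.** Two-sided alpha 5%, two-sample t-test; MORS-SF d = 2.35 / 4.7 = 0.50; PHQ-8/GAD-7 d = 0.42; attrition 40%; minimums 45 and 62; targets 72 and 99. All come from the sample size sections. Power is from the noncentral t distribution.

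**1. The plan's figures before attrition reproduce.**

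| Outcome | Split | Power |
|---|---|---|
| MORS-SF, d = 0.50 | 65:65 | 80.8% |
| | 56:84 | 82.1% |
| | 50:100 | 81.8% |
| | 45:135 | 82.4% |
| PHQ-8/GAD-7, d = 0.42 | 95:95 | 82.1% |
| | 80:120 | 82.5% |
| | 70:140 | 81.5% |
| | 62:187 | 81.5% |

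Every split reaches 80%, most with a little slack. The problem is confined to the inflation step.

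**2. The inflation step does not reproduce.**

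- Women left: 72 × 0.6 = 43.2 (45 stated); 99 × 0.6 = 59.4 (62 stated).
- Enrolment needed: 45 / 0.6 = 75; 62 / 0.6 = 103.3, rounded up to 104.

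**3. What would give 72 and 99.**

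- n × 1.4: 63 and 86.8. Neither matches.
- n × 1.6: 72.0 and 99.2. Both match.
- Attrition implied by the printed pairs: 1 − 45/72 = 37.5%; 1 − 62/99 = 37.4%.

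Multiplying by 1.6 and assuming attrition of 37.5% are the same calculation, because 1 / 1.6 = 0.625. The numbers alone cannot separate a formula slip from a rate rounded up for the text.

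**4. Power with the women actually left.**

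| Outcome | Intervention:control | Power |
|---|---|---|
| MORS-SF, 72 enrolled | 43:129 | 80.6% |
| MORS-SF, 99 enrolled | 59:177 | 91.2% |
| | 59:70 | 80.2% |
| | 59:59 | 76.8% |
| PHQ-8/GAD-7, 99 enrolled | 59:187 | 80.0% |
| | 59:177 | 79.5% |
| | 59:118 | 74.5% |
| | 59:59 | 61.9% |

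The 59:187 row keeps the plan's own number of controls. The 59:177 row keeps a strict 1:3 ratio. Controls come from the cohort and cannot drop out of Baby Steps, so 59:187 is a fair reading if that many can be matched.

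**5. Intention to treat.** If all 99 enrolled mothers are analysed, even 99:99 gives 83.7% at d = 0.42 and 93.8% at d = 0.50, before any outcome non-response and assuming the same effect size in non-completers.

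**The case against.** The strongest reply is that little follows. The advice to recruit 99 supersedes the 72, and 99 leaves 59 completers against 45 needed for the primary outcome. The shortfall on the secondary outcomes is about three women, and with 187 controls power is still 80.0%. All of this stands, and it sets the size of the point.

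It can also be said that approximately 40% may stand for 37.5%. That is possible, and for this reason the cause should not be stated as a known error. It does not rescue the text, because the mental health section applies the 40% rate without qualification. A reader using that rate cannot arrive at the printed result.

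The dependence on the number of controls is disclosed: both sections make the smaller intervention numbers conditional on a larger control group, and one-to-many matching is planned. What remains is only that the enrolment sentences drop the condition.

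Two stronger readings are tempting, and the documents do not support them:

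- **That the study falls well short of its minimums if controls are fewer than 3:1.** For the MORS-SF, 59 completers need only about 70 controls for 80% power. Marked sensitivity to the ratio is limited to PHQ-8/GAD-7 among completers.
- **That the analysable number falls much further once cohort membership and questionnaire response are also discounted.** The protocol gives no rate for either. It defines study participants as women already in the cohort, plans multiple imputation when missing outcome data exceed 5%, and keeps non-completers in the intention-to-treat analysis. Multiplying these losses together is not justified by the text.

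**Conclusion.** The enrolment figures are wrong as written: at 40% attrition, 72 and 99 yield about 43 and 59, not 45 and 62. The correct inflation gives 75 and 104. This needs only the protocol's own numbers.

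The consequence is minor. At the recommended 99, the primary-outcome minimum of 45 is met with room to spare and only the secondary-outcome minimum of 62 is missed. The cost there is 1.5 to 2 percentage points of completer power, from 81.5% to between 79.5% and 80.0% at about three controls per woman. The loss becomes material for PHQ-8/GAD-7 only with fewer controls, and then only in the per-protocol analysis.

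These powers assume the protocol's effect sizes and a plain two-sample t-test, and treat programme non-completion as the only loss.

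Separately, the closing sentence of the mental health section contradicts the MORS-SF section. It claims power for a minimum clinically important difference on a scale for which the protocol says none is available.

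**What to change.** 1. In the two sample size sections, do one of the following:
   - replace 72 by 75 and 99 by 104;
   - keep 72 and 99 and state the attrition rate actually used, if it was nearer 37.5%;
   - keep 99, state that it yields about 59 completers, and give PHQ-8/GAD-7 power of about 79.5% at 59:177 or 80.0% at 59:187, 74.5% at 59:118 and 61.9% at 59:59.
2. Where 45 and 62 are called minimums, add that they hold only at about three matched controls per intervention woman. This also reconciles them with the 1:1 minimum of 130 in the abstract.
3. State that the 40% is programme non-completion, so the inflated target bears directly on the per-protocol analysis, while the intention-to-treat analysis keeps all enrolled mothers.
4. Reword the closing sentence to claim power for a 2-point difference on PHQ-8 and GAD-7 and for 0.5 SD on the MORS-SF.

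The cost is a few sentences. If 104 is adopted, the service is asked for five more enrolments than it was told (104 − 99 = 5). No design or analysis change is needed.

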#### Maternal mental health (GAD-7 and PHQ-8)

Recent studies have estimated the minimum clinically important difference in the PHQ-9 to be 2 points [5, 32]. The sample size calculations show that we will have 80% power to detect this difference in the PHQ-8 and GAD-7 (± 2, *d* = 0.42) with 190 participants total (95:95), or if we obtain a larger control group through the BiBBS cohort (e.g. 200 total (80:120), 210 total (70:140), 250 total (62:187)). With the 40% attrition rate, Baby Steps should aim to enrol at least 99 participants to achieve the minimum sample size of 62 participants at the end of the study. We have therefore recommended to Baby Steps that they aim to recruit 99 intervention participants overall, as after accounting for attrition, this study should have statistical power to detect a minimum clinically important difference in all measures (MORS-SF, PHQ-9, GAD-7).

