### Data collection procedures

The study will include all women recruited from 1^st^ May 2022, up until the end of the delivery of the service (anticipated to be at the end of 2023).

Pregnant women complete a detailed questionnaire when recruited to BiBBS regarding their prenatal attachment, mental health, socio-demographics, family circumstances and more. Data provided from this questionnaire will enable intervention and control groups to be matched, where individual intervention participants can be matched to > 1 control group participant(s) (see statistical methods section for details).

All BiBBS mothers will complete outcome measures at 6–10 weeks after birth. The data are collected either by phone or at a physical home visit. The questionnaires include: the Patient Health Questionnaire-8 (PHQ-8), Generalised Anxiety Disorder assessment-7 (GAD-7), and the Mothers Object Relations Scale-Short Form (MORS-SF) (see below for details).

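### The enrolment targets of 72 and 99 rest on 1:3 allocations that the protocol makes conditional, but its closing power claim drops the condition and the Abstract states a different minimum

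*Protocol article*

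**What the plan says.** All references are to the protocol article.

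- **Sample size calculations, MORS-SF.** For d = 0.50 the section lists 65:65 and then, if more controls are obtained, 56:84, 50:100 and 45:135. It cites about 40% attrition between enrolment and completion and continues: "Baby Steps should therefore aim to enrol at least 72 participants to achieve the minimum sample size of 45 participants in the intervention group".
- **Sample size calculations, GAD-7 and PHQ-8.** For d = 0.42 it gives 95:95, "or if we obtain a larger control group through the BiBBS cohort (e.g. 200 total (80:120), 210 total (70:140), 250 total (62:187"). From the last of these it takes 62 as the minimum and 99 as the enrolment target. It recommends 99 overall because, "after accounting for attrition, this study should have statistical power to detect a minimum clinically important difference in all measures".
- **Abstract, Methods.** "The required minimum sample is *n* = 130 (ratio 1:1) to detect a medium effect" on the primary outcome.
- **Data collection procedures.** "individual intervention participants can be matched to > 1 control group participant(s"). The Propensity score matching section says that one-to-many matching will be used to maximise power. Neither section fixes a ratio or a minimum number of controls.
- **Linear regression analyses.** The ITT analysis keeps every mother who enrolled after the initial home visit. The per-protocol analysis keeps completers only.

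**The concern.** The only rows listed without a condition are the 1:1 rows. The enrolment targets use the opposite end of each list, where the intervention arm is smallest and about three controls per mother are assumed. The concluding sentence, which is also the recommendation passed to the delivery service, gives no control number. A reader would take 99 enrolled as sufficient in itself.

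If matching yields fewer controls than the 1:3 rows assume, a null result on PHQ-8 or GAD-7 would be read against a claimed 80% power that the study did not have. The Abstract adds to the difficulty by giving a minimum from a different row (65 mothers) than the one behind the targets (45 or 62). The article gives no estimate of how many eligible controls there will be. Under Eligibility, a control must have outcome data and must never have received a programme that is now offered to all pregnant women in the area.

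**Working it through.** **Inputs.** Two-sample t-test, two-sided 5% (Sample size calculations). MORS-SF: SD 4.7, difference 2.35, d = 0.50. PHQ-8/GAD-7: difference 2, d = 0.42. Attrition 40%.

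**Formula.** With n1 mothers and n2 controls, the noncentrality is d / √(1/n1 + 1/n2) on n1 + n2 − 2 degrees of freedom. Power is the probability that the noncentral t variable exceeds the two-sided 5% critical value.

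**Step 1: the printed rows.** They reproduce.

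- MORS-SF: 65:65 gives 80.8%, 56:84 82.1%, 50:100 81.8%, 45:135 82.4%.
- PHQ-8/GAD-7: 95:95 gives 82.1%, 80:120 82.5%, 70:140 81.5%, 62:187 81.5%.

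Each listed allocation is therefore sound.

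**Step 2: retained counts.** At 40% loss, 72 × 0.6 = 43.2 and 99 × 0.6 = 59.4, so 43 and 59 mothers remain, not 45 and 62. Keeping 45 and 62 would need 45/0.6 = 75 and 62/0.6 = 103.3, rounded up to 104. The printed targets equal 45 × 1.6 = 72 and 62 × 1.6 = 99.2. This corresponds to a loss of 1 − 45/72 = 37.5%.

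**Step 3: power by ratio.**

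| Outcome, mothers retained | 1:1 | 1:2 | 1:3 | Controls for 80% |
|---|---|---|---|---|
| PHQ-8/GAD-7, 62 (as printed) | 64% | 77% | 81% | 163 (2.6 each) |
| PHQ-8/GAD-7, 59 (40% loss) | 62% | 75% | 79.5% | 187 (3.2 each) |
| MORS-SF, 45 (as printed) | 65% | 78% | 82% | 109 (2.4 each) |
| MORS-SF, 43 (40% loss) | 63% | 76% | 81% | 122 (2.8 each) |

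Example: for 62:62 the noncentrality is 0.42 / √(2/62) = 2.34 on 122 degrees of freedom, and power is 64%.

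**Step 4: MORS-SF at the recommended 99.** At 1:1, 59:59 gives 77% and 62:62 gives 79%. Reaching 80% takes 70 controls for 59 mothers (1.19 each) or 66 for 62 mothers (1.06 each).

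**Step 5: the Abstract.** 130 at 1:1 is 65 mothers. After attrition 72 leaves 43 to 45 and 99 leaves 59 to 62, so neither reaches 65. On the same accounting, a 1:1 design would need 65/0.6 = 108.3, so 109 enrolled for MORS-SF, and 95/0.6 = 158.3, so 159 for PHQ-8/GAD-7.

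**Step 6: the other bound.** If every enrolled mother gives outcome data, 1:1 power is 85% for MORS-SF with 72 (72:72), 94% for MORS-SF with 99 (99:99) and 84% for PHQ-8/GAD-7 with 99.

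**The case against.** Much can be said for the protocol. Both paragraphs state the condition and print each allocation before the concluding sentence, and that sentence is hedged. One-to-many matching is the declared plan, so 1:1 is a worst case; at 1:2 with 62 mothers the shortfall for PHQ-8/GAD-7 is only about 3 points. The Abstract's 130 is labelled 1:1 and is a correct figure for that row.

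Three stronger readings are tempting, and the documents do not support them.

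- *Three controls per mother are strictly required.* On the printed counts 80% is reached at about 2.4 (45 mothers) or 2.6 (62 mothers). Three is the row the protocol chose, not the threshold.
- *The targets cannot supply 65 mothers.* This holds only if programme non-completers have no outcome data. The 40% is loss from the programme. Data collection procedures plans outcome measures for all mothers in the cohort, and the ITT analysis keeps all who enrolled. With full follow-up both targets exceed 65.
- *The primary outcome is badly underpowered.* The figure of 65% belongs to 72 enrolled at 1:1. The recommendation is 99, for which MORS-SF needs only 1.1 to 1.2 controls per mother.

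What remains is that the protocol itself removes the attrition before claiming power, names no analysis population for the claim, and drops the control numbers from its conclusion.

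**Conclusion.** The point holds as a matter of an unstated condition and unaligned figures; the listed allocations are not wrong. On the protocol's attrition accounting, the claim for PHQ-8/GAD-7 needs about 2.6 controls per mother with 62 retained, or 3.2 with the 59 that a 40% loss leaves. At 1:1 power is 62% to 64%, some 16 to 18 points below the 80% claimed, and at 1:2 it is 75% to 77%. For MORS-SF at 99 enrolled the gap is at most about 3 points, and only at 1:1.

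These are in effect figures for completers. The article does not state the loss of outcome data. Provided that loss is no more than 40%, ITT power for PHQ-8/GAD-7 with 99 enrolled at 1:1 lies between 62% and 84%. All figures use the protocol's own t-test and effect sizes.

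**What to change.** 1. In the GAD-7 and PHQ-8 sample size paragraph, make the closing claim conditional on the number of matched controls with outcome data, and give power at 1:1, 1:2 and 1:3 (table above). Do the same for MORS-SF.
2. Correct the retained counts to 43 and 59, or restate the attrition as 37.5% if 45 and 62 are to stand. Use the matching rows of the table.
3. Say whether the attrition applies to the ITT or the per-protocol population. If to the latter only, state the expected loss of outcome data for the ITT analysis.
4. Align the Abstract with the allocation that the targets assume, or say that 130 suffices only with 65 intervention mothers with outcome data.

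The cost is a few sentences and a small table, with no extra participants. The stated power becomes conditional, and less favourable below about 1:3.

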#### Secondary outcomes measures (maternal mental health)

##### Patient Health Questionnaire (PHQ-8) and Generalised Anxiety Disorder Assessment (GAD-7) questionnaires

The PHQ-9 and GAD-7 are widely used tools to assess depression and anxiety, respectively [33, 47]. They have previously been used as outcome measures in parenting programme trials [8]. The PHQ-9 has been found to successfully differentiate between depressed and non-depressed mothers, supporting its use to screen for postpartum depression [26].

BiBBS uses the PHQ-8, which is also a widely used tool to assess depression and only differs to the PHQ-9 in that it omits Item 9 [34]. Item 9 of the Patient Health Questionnaire-9 (PHQ-9) queries about thoughts of death and self-harm. Validation studies have found that both the PHQ-9 and PHQ-8 have similar diagnostic properties [44, 54]. To compare the PHQ-8 outcomes, any participants with a PHQ-9 questionnaire will have data dropped for Item 9.

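### Power is claimed for a minimum clinically important difference in all measures, though the article has none for the MORS-SF and sources one only for the PHQ-9; the enrolment targets of 99 and 72 also fall short of the plan's own attrition rate

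*Protocol article*

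**What the plan says.** All places are in the protocol article, under Sample size calculations unless stated.

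- **MORS-SF (primary outcome).** The paragraph opens "In the absence of a minimum clinically important difference for the MORS-SF" and uses half a standard deviation instead. With an SD of 4.7 this is 2.35 points, d = 0.50. The sample is 65:65, or fewer intervention mothers with more controls, down to 45:135. Enrolling 72 is said to leave 45 after 40% attrition.
- **PHQ-8 and GAD-7.** "Recent studies have estimated the minimum clinically important difference in the PHQ-9 to be 2 points". The next sentence applies the same 2 points (d = 0.42) to the PHQ-8 and to the GAD-7. The sample is 95:95, or fewer intervention mothers with more controls, down to 62:187. Enrolling 99 is said to leave 62 after 40% attrition.
- **Conclusion.** With 99 recruited and attrition allowed for, the study should have "statistical power to detect a minimum clinically important difference in all measures (MORS-SF, PHQ-9, GAD-7").
- **Scale used.** The secondary-outcomes section says "BiBBS uses the PHQ-8". It adds that the PHQ-8 differs from the PHQ-9 only in omitting item 9, that the two have similar diagnostic properties, and that item 9 will be dropped for anyone who has a PHQ-9.

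**The concern.** The concluding sentence claims something that the preceding paragraph rules out. A study cannot be shown to have power for an MCID on the MORS-SF when its authors say that none is available. For the GAD-7, a different scale measuring anxiety, no MCID is given or cited. So for two of the three measures listed, the claim has no basis in the article. The sentence also names the PHQ-9, although the analysed scale is the PHQ-8.

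The same sentence says that attrition has been allowed for, but the enrolment targets do not deliver the retained numbers they are meant to deliver.

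At stake are the accuracy of the headline power claim, including for the primary outcome, and the recruitment target passed to the service. The Discussion says that a finding of ineffectiveness may lead services to reconsider the delivery format, so how a null result is described matters.

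**Working it through.** **Inputs.** Two-sample t-test, two-sided 5% (Sample size calculations). MORS-SF: SD 4.7, difference 2.35, so d = 2.35/4.7 = 0.50. PHQ-8 and GAD-7: difference 2, d = 0.42, which implies one unstated SD of 2/0.42 = 4.76 for both scales. Attrition 40%.

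**Power formula.** Noncentral t with n1 + n2 − 2 degrees of freedom and noncentrality d × √(n1·n2/(n1 + n2)).

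**Step 1: the plan's own figures.** Example: for 62:187 at d = 0.42, the noncentrality is 0.42 × √(62 × 187/249) = 2.866. With 247 degrees of freedom and a critical value of 1.970, power is 81.5%.

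| Measure | Sample | Power |
|---|---|---|
| MORS-SF, d = 0.50 | 65:65 | 80.8% |
| | 56:84 | 82.1% |
| | 50:100 | 81.8% |
| | 45:135 | 82.4% |
| PHQ-8/GAD-7, d = 0.42 | 95:95 | 82.1% |
| | 80:120 | 82.5% |
| | 70:140 | 81.5% |
| | 62:187 | 81.5% |

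Every stated scenario reaches 80%. At 62:187 the MORS-SF has 92.5% power for d = 0.50.

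**Step 2: which of these differences is an MCID in the article?**

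| Measure | Difference powered for | MCID in the article |
|---|---|---|
| MORS-SF | 2.35 points (0.5 SD) | Said to be unavailable |
| PHQ-8 | 2 points | PHQ-9 value, with supporting text for treating the scales alike |
| GAD-7 | 2 points | None; PHQ-9 value carried over without a reason |

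**Step 3: attrition.** Retained = enrolled × (1 − 0.40), so enrolled = retained/0.60.

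| Needed | Stated enrolment | Retained at 40% loss | Enrolment required |
|---|---|---|---|
| 62 | 99 | 99 × 0.6 = 59.4 | 62/0.6 = 103.3, so 104 |
| 45 | 72 | 72 × 0.6 = 43.2 | 45/0.6 = 75 |

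The stated targets equal the needed number × 1.6 (62 × 1.6 = 99.2; 45 × 1.6 = 72.0), where division by 0.6 is required.

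**Step 4: effect of the shortfall on power.**

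| Retained:controls | d = 0.42 | d = 0.50 |
|---|---|---|
| 59:187 | 80.0% | 91.6% |
| 59:177 | 79.5% | 91.2% |
| 59:118 | 74.5% | 87.7% |
| 59:59 | 61.9% | 76.8% |
| 43:135 | n/a | 81.1% |

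With about three controls per intervention mother the shortfall costs little. With fewer controls, power for the 2-point difference falls below 80%.

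**The case against.** The best reply is that this is a labelling slip. The MORS-SF paragraph openly says that no MCID exists, names its substitute and cites a source for it; the later sentence loosely sums up targets already set out. All the power figures hold, and the primary outcome is better powered at 62:187 than the plan says. Controls come from the cohort, so losing intervention mothers does not shrink the control pool, and 59:187 still gives 80.0%. All of this stands, and it limits the size of the point. It does not make the concluding sentence true, and that sentence does not say that its power depends on having about three controls per mother.

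Four stronger readings are tempting but not supported:

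- **That the plan tells commissioners a null result rules out an important effect.** No sentence says so. The Discussion says only that teams may need to consider in-person formats. The risk is an inference.
- **That the MORS-SF label drives the target of 99.** It does not. The 99 comes from the 62 needed for the PHQ-8 and GAD-7; the MORS-SF figures are 45 and 72.
- **That no PHQ-9 data exist, or that the carry-over to the PHQ-8 is unfounded.** The secondary-outcomes section allows for some PHQ-9 questionnaires and gives grounds for treating the two scales alike. Only the name in the sentence needs correcting.
- **That the study is underpowered because power is low at 0.2 or 0.3 SD.** The plan sets neither as a target, and any study has low power below its target.

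**Conclusion.** The point holds as an error of statement and of arithmetic. It is not a failure of the power calculations. The claim of power for an MCID contradicts the article for the MORS-SF and has no stated basis for the GAD-7. The enrolment targets are 5 short (99 against 104) and 3 short (72 against 75) at the plan's own attrition rate.

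The numerical effect is small if the controls materialise: 81.5% falls to 80.0% at 59:187 for d = 0.42, and the MORS-SF keeps about 92% for d = 0.50. It is larger if they do not: 74.5% at 59:118 and 62% at 59:59 for d = 0.42. Those two samples are illustrations. The plan's own 1:2 and 1:1 options start from 70 and 95 intervention mothers.

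This rests on the plan's unadjusted two-sample t-test, its d of 0.42 for both mental-health scales, and its own use of 40% as the loss from enrolled to analysed. Whether 2.35 points on the MORS-SF or 2 points on the GAD-7 lies above or below a true MCID cannot be judged from the article.

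**What to change.** Replace the concluding sentence and correct the two enrolment statements, as follows:

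1. **MORS-SF:** power is for 0.5 SD (2.35 points), a conventional difference used because no MCID is known. Power is about 82% at 45:135 and about 92% at 62:187 or 59:187.
2. **PHQ-8 (not PHQ-9) and GAD-7:** power is for 2 points (d = 0.42), a PHQ-9 value carried over and, for the GAD-7, an assumption. Power is 81.5% at 62:187.
3. **Attrition:** 99 enrolled leaves about 59 at 40% loss. That gives about 80% power for d = 0.42 only with about three controls each (79.5% at 59:177, 80.0% at 59:187), against 74.5% at 59:118 and 62% at 59:59. Retaining 62 needs 104 enrolled. For the MORS-SF, 72 leaves 43, and retaining 45 needs 75.
4. **Interpretation:** drop the claim of power for an MCID in all measures, and say that a null MORS-SF result will not be read as excluding a clinically important effect.

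The cost is a change of text and a slightly less favourable power claim. Test, outcomes and analysis stay as they are. If the retained numbers of 62 and 45 are to be kept, the targets rise by 5 and 3 mothers.
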